# Team based collaborative care model, facilitated by mHealth enabled and trained nurses, for management of heart failure with reduced ejection fraction in India (TIME-HF): design and rationale of a parallel group, open label, multi-centric cluster randomised controlled trial

**DOI:** 10.12688/wellcomeopenres.19196.2

**Published:** 2023-07-12

**Keywords:** Heart failure, collaborative care model, mhealth application, cluster randomised controlled trial

## Abstract

**Background: **Heart failure (HF) is a debilitating condition associated with enormous public health burden. Management of HF is complex as it requires care-coordination with different cadres of health care providers. We propose to develop a team based collaborative care model (CCM), facilitated by trained nurses, for management of HF with the support of mHealth and evaluate its acceptability and effectiveness in Indian setting.

**Methods: **The proposed study will use mixed-methods research. Formative qualitative research will identify barriers and facilitators for implementing CCM for the management of HF. Subsequently, a cluster randomised controlled trial (RCT) involving 22 centres (tertiary-care hospitals) and more than 1500 HF patients will be conducted to assess the efficacy of the CCM in improving the overall survival as well as days alive and out of hospital (DAOH) at two-years (CTRI/2021/11/037797). The DAOH will be calculated by subtracting days in hospital and days from death until end of study follow-up from the total follow-up time. Poisson regression with a robust variance estimate and an offset term to account for clustering will be employed in the analyses of DAOH. A rate ratio and its 95% confidence interval (CI) will be estimated. The scalability of the proposed intervention model will be assessed through economic analyses (cost-effectiveness) and the acceptability of the intervention at both the provider and patient level will be understood through both qualitative and quantitative process evaluation methods.

**Potential Impact:** The TIME-HF trial will provide evidence on whether a CCM with mHealth support is effective in improving the clinical outcomes of HF with reduced ejection fraction in India. The findings may change the practice of management of HF in low and middle-income countries.

## Introduction

Globally, heart failure (HF) is a major public health problem with relatively high morbidity and mortality. The number of individuals with HF is estimated to be in the range of 1.3 to 4.6 million in India
^
1–
3
^. Additionally, the number of deaths due to HF in India showed an increase of 138 percent from 1990–2013
^
2
^. Based on the best available estimates, the incidence of HF in India is 1 per 1000 population
^
2
^. In consistent with findings from many high-income countries, the predominant etiology of HF is ischemic heart disease (IHD) in India
^
4
^. Due to the steady increase in the absolute number of individuals with IHD over the last three decades
^
5,
6
^, HF burden is expected to grow substantially in India.

Heart failure patients in India receive sub-optimal treatment and experience high mortality. For example, only one of four eligible HF patients receives guideline-directed medical therapy (GDMT) at discharge
^
2,
7
^. Similarly, one of three patients adhered to GDMT in a large study in India involving 15,870 patients with reduced left ventricular ejection fraction (EF<40%)
^
8
^. Additionally, one of five patients died within three months of follow-up
^
2
^. The long-term prognosis of HF is also poor with a median survival time of 3.7 years
^
9
^. However, those who received GDMT experienced lower mortality and survived longer
^
2
^. Data from the Kerala Heart Failure Registry
^
10
^, and the National Heart Failure Registry
^
4
^ also demonstrated survival benefits in patients who received GDMT during index hospitalisation. Further, the survival benefits of GDMT persisted up to five years of follow-up
^
9
^.

Physician driven quality improvement initiatives in HF management may not be feasible, scalable, and effective in India. The PINNACLE India quality improvement programme concluded that in a country with a disproportionate provider/patient ratio and low levels of government funding for quality improvement, physician-driven initiatives for practice-based learning and improvement are extremely difficult
^
11
^. The key barriers include lack of electronic medical records, virtually non-existent outpatient record-keeping, and difficulty of engaging physicians due to their busy clinical schedules
^
11
^. To overcome these barriers, we propose a task sharing strategy of empowering trained nurses as facilitators of HF care in India.

A specially trained nurse facilitating the management is a viable alternative strategy in the management of HF
^
12–
15
^. In general, specialist HF nurses share the role of a physician, assess the patients, and manage them based on the tested protocols/algorithms. Additional roles for nurses include psycho-social aspects of self-management of the condition in home settings
^
16
^, communicating self-care guidelines
^
15
^, and regular monitoring of patient conditions even when they are away from the hospital or outpatient settings. These strategies in general are effective in achieving improved physical functioning, reduced hospital length of stay and increased adherence towards pharmacological therapy in high-income settings. Three recent meta-analyses also show that task sharing strategy, especially involving nurses in management of cardiovascular risk conditions such as hypertension
^
17
^, dyslipidemia
^
18
^ and diabetes
^
19
^ is effective in achieving desirable outcomes even in low and middle-income countries (LMIC).

The collaborative care model (CCM) based on Wagner’s Chronic Care Model
^
20
^ is proposed as a key strategy in the management of HF. For example, CCM results in improvements in hospitalisation rates
^
21,
22
^ and quality of life
^
23
^, and reduction in cost associated with management of HF
^
24–
27
^. Additionally, increased use of GDMT and improved self-care are also attributed to interventions based on CCM
^
28,
29
^. However, most of them are small single centre studies leading to reduced validity and reliability of their findings. We propose to develop a CCM, facilitated by trained nurses, for management of HF with reduced ejection fraction (HFrEF) and evaluate its acceptability and effectiveness in Indian settings.

The major aims of the study are as follows: (1) to identify barriers and facilitators for implementing a team based CCM for the management of HF, (2) to assess the efficacy of the CCM in improving the days alive and out of hospital (DAOH) at two-year follow up in patients with HFrEF and (3) to evaluate the scalability of proposed intervention model; (a) to evaluate the overall
*cost-effectiveness* of the intervention strategy, (b)
*at the provider level*, to assess the ease of using the protocols/mHealth application, impact on work load, and satisfaction, and (c)
*at the patient level*, to explore risk-perception, ease of seeking health care, utility of understanding risk and addressing warning signs/symptoms on a real time basis, changes made to health behaviours and adherence to guideline directed therapies.

## Methods

### Ethical considerations

The participants will be informed about the study and provided with a detailed information sheet
^
30
^. Trained research nurse appointed by the principal investigator will obtain written informed consent from all study participants. The research study is approved by institutional ethics committee of Sree Chitra Tirunal Institute for Medical Sciences and Technology (SCTIMST) and of the participating centres (SCT/IEC/1691/AUGUST-2021). The study protocol is registered with the clinicaltrials.gov (CTRI/2021/11/037797). All changes in the trial protocol will be informed to the institutional review boards.

All serious adverse events will be reported immediately to the respective ethics committees of the participating centres and the study co-ordinating centre (SCTIMST). The principal investigators (PIs) will have access to the final data set. Public access to the data set after de-identification will be provided upon formal request with necessary permission from the SCTIMST ethics committee after three years from the date of completion of the study.

### Study design approach

The proposed study will use mixed methods to achieve the study aims. The design approaches will include: Aim 1- formative qualitative research, Aim 2- a multi-centric cluster randomised controlled trial (RCT), and Aim 3- cost effectiveness and evaluative qualitative research. We will follow the Medical Research Council (UK) guidance on developing and evaluating complex interventions
^
31
^ and guidance for reporting intervention development studies in health research
^
32
^. The trial duration will be from September 2021 to August 2026
^
33
^.

The protocol design is based on the Standard Protocol Items: Recommendations for Intervention Trials (SPIRIT) Checklist
^
34
^. The SPIRIT flow chart shows the schedule of enrolment, interventions, and assessments of TIME-HF trial
^
35
^.

**
*Formative qualitative research (Aim 1)*
**

In-depth interviews with multiple stakeholders like patients, carers, nurses, community health workers, primary care physicians, and cardiologists will be conducted (
Table 1). Interviews with nurses and cardiologists will be face-to-face, semi-structured and include questions regarding HF care integration. Additional in-depth interviews will be conducted with dieticians, specialist physiotherapist and clinical psychologists to get their perceptions of CCM. In-depth interviews with adult HF patients will gather information on their understanding of diseases, barriers and facilitators to care, and feedback on the proposed intervention components (lifestyle education, disease management program, pharmacologic treatment, self-care, and care coordination). Similarly, in-depth interviews of adult carers of patients with HF will gather information on self-management and care coordination. The number of interviews will be determined based on thematic saturation in each category. The stakeholders for the interview will be selected from hospitals with facilities for management of HF. The intervention and trial protocols will be modified by incorporating key findings from the qualitative study.

**Table 1. T1:** Formative qualitative methods.

Participants	Methods/Number	Topics
Patients with HF both male and female in various age groups	In-depth interview Total 10–12 IDIs	● Perceptions and behaviours on clinical management, lifestyle, and self-care ● Feedback on proposed intervention components and methods ● Assess patients’ interest and acceptability
Caregivers of patients with HF	In-depth interview Total 10–12 IDIs	● Perceptions and behaviours on clinical management, lifestyle, and self-care ● Feedback on proposed intervention components and methods ● Gauge caregivers’ interest and acceptability
Physicians Nurses Dieticians Physiotherapists	In-depth interview 10–12 interviews in each category (30–36 total interviews)	● Perceived quality of HF care ● Perceived patient barriers and facilitators to delivery of care, lifestyle change, and self-care ● Gauge feasibility of planned intervention components

**
*Collaborative care model intervention (Aim 2)*
**

A parallel group cluster RCT of more than 1500 adult HF patients with reduced ejection fraction from 22 units in India
^
36
^ will be used to address Aim 2. Each participating unit will be randomly assigned to one of two arms: 1) those delivering a comprehensive CCM (intervention) or 2) those delivering standard of care (usual care).

The selected hospitals will be independent units with dedicated staff employed at each site for recruitment and follow-up of patients included in the trial. The site teams will have similar compositions in terms of clinical roles.

Cluster eligibility criteria: Eligible units will include HF centres of major hospitals from the national heart failure registry or Kerala heart failure registry that serve ≥80 new patients in six-months and consented to the randomisation plan. All HF patients will also be required to provide individual consent to participate in the study.

Patient eligibility criteria and randomisation: Potential participants must meet the standard definition of HF
^
37
^ (HF with reduced ejection fraction of <40%) based on echocardiography to be eligible to enter the study. Consecutive patients will be recruited from the participating centres. Eligible units will be randomised at one time point, prior to trial implementation. The allocation ratio will be 1:1. Randomisation procedures will not be blocked, restricted, or matched. We will use computer generated random numbers to allocate half of the units to each arm of the study.

*Duration of treatment period and follow-up*

We will conduct a rolling recruitment over a period of six-twelve months. Each patient in the study will be followed-up for a period of two years from the date of recruitment. The first follow-up visit in the intervention arm will be conducted on the seventh day. Additional two follow-up visits for clinical status occurs at an interval of three-months. Participants are subsequently seen no less than every six months. Regardless of the treatment group assigned, we will follow-up all study participants in this manner (assessment at 7-th day will be only in the intervention arm) until study completion.

*Measurements in the study*

A structured questionnaire
^
38,
39
^ will be administered by trained research nurse to collect relevant data at baseline, and every three months until two years from baseline. At these visits, interval assessments of HF and angina symptom status, current use of medications, and clinical endpoint data including hospitalisations and procedures since the previous visit will be documented (
Table 2). The baseline questionnaire includes assessments of demographic and socio-economic variables, general health status, aetiology, history and risk factors, diet pattern, physical activity, tobacco, and alcohol consumption, quality of life, and six minutes walking distance. Depression and anxiety scores will be collected from each participant by using Patient Health Questionnaire- 9 (PHQ-9)
^
40
^ and Generalized Anxiety Disorder Questionnaire (GAD-7) at baseline and during follow-up visits
^
41
^. Medication adherence will be measured using four item Morisky Green Levine medication adherence scale during the follow-up visits
^
42
^. The follow-up study questionnaire will also assess the patient satisfaction in quality of care, and family support.

**Table 2. T2:** Study measurements in TIME-HF.

Study measurements	Method/Instrument
Blood pressure in mmHg	Electronic BP monitor
Height in cm	Stadiometer
Weight in kg	Digital weighing scale
Waist circumference in inches	Non elastic measuring tapes
Etiology and risk factors	Details of the etiology and risk factors using a questionnaire
Investigations	Blood reports, ECHO, ECG reports
Current Medication	Details of all medications the patient was taking at the time of contact
Depression	PHQ-9 ^ 40 ^
Anxiety	GAD-7 ^ 41 ^
Self-management Medication adherence, weight, family support, diet, depression care	Morisky, Green and Levine medication adherence scale ^ 42 ^, weight management ^ 38 ^, Diet Management ^ 38 ^, Family support ^ 38 ^; Patient care in depression ^ 38 ^
Quality of life	KCCQ ^ 43 ^, EQ-5D-5L ^ 44, 45 ^
Walking ability	6 Minute Walk Test ^ 46 ^
Physical disability (muscular strength)	Hand grip strength- Dynamometer
Frailty	Fried frailty index ^ 47, 48 ^
Functional capacity	Specific Activity Questionnaire ^ 38 ^
Physical activity intensity	The Borg Scale of Perceived Exertion ^ 49 ^
Disease severity	Modified Borg Dyspnea Scale during 6MWT (0 – 10) ^ 50, 51 ^, Responsiveness to change in heart failure symptoms ^ 38 ^
Treatment burden	MTBQ ^ 52 ^
Patient satisfaction	Patient satisfaction in Quality of care ^ 38 ^, Care transitions measure (CTM3) ^ caretransitions.org/ ^, B-Prepared Scale ^ 53 ^

PHQ-9- Patient Health Questionnaire- 9, GAD-7- Generalised Anxiety Disorder Questionnaire, KCCQ-Kansas City Cardiomyopathy Questionnaire, EQ-5D-5L -EuroQoL 5dimension -5 level ,6MWT- Six Minute Walk Test, MTBQ- Multi-morbidity Treatment Burden Questionnaire, ECHO -Echocardiogram, ECG -Electrocardiogram

Kansas City Cardiomyopathy Questionnaire (KCCQ)
^
43
^ and EQ-5D-5L
^
44
^ will be used to measure quality of life.

A standard adjustable handgrip dynamometer will be used to measure handgrip strength. Three measurements will be taken in dominant and non-dominant hand. The average of the highest value of dominant and non-dominant handgrip strength will be used in the analysis.

The six-minute walk test (6MWT) will be measured during the baseline and follow-up visits by following the standard protocol
^
46
^. Before the 6MWT, the research nurse will measure blood pressure, pulse, and oxygen saturation with the help of a pulse oximeter. During the test, participants will have to walk for six minutes. After the test, staff will record the distance covered along with oxygen level, pulse rate and post walk Borg dyspnoea levels.

Treatment burden will be assessed by using multimorbidity treatment burden questionnaire (MTBQ)
^
52
^. Health care expenditure data will be collected every six months using a treatment expenditure questionnaire
^
38
^. Clinic based blood pressure will be obtained during clinic visits. Blood will be collected at six-month interval to assess renal function and serum electrolytes. Further, we will collect data on beta-natriuretic peptides at baseline, and follow-up visits, if they are routinely done as part of the patient care. The detailed study measurements at baseline and during the study period are explained in
Table 3.

**Table 3. T3:** Measurement of different parameters at baseline (B), and during follow-up at 3 months (F 3M), 6 months (F 6M), 9 months(F 9M), 12 months(F 12M), 15 months(F 15M), 18 months(F 18M), 21 months(F 21M), 24 months(F 24M).

Study Measurements	B	F 3M	F 6M	F 9M	F 12M	F 15M	F 18M	F 21M	F 24M
Blood Pressure (in mmHg)	✔	✔	✔	✔	✔	✔	✔	✔	✔
Height (in cm)	✔	✔	✔	✔	✔	✔	✔	✔	✔
Weight (in kg)	✔	✔	✔	✔	✔	✔	✔	✔	✔
Waist circumference (in inches)	✔	✔	✔	✔	✔	✔	✔	✔	✔
PHQ-9	✔				✔		✔		✔
Patient care in depression	✔	✔	✔	✔	✔	✔	✔	✔	✔
KCCQ 12	✔				✔		✔		✔
GAD-7	✔				✔		✔		✔
Morisky, Green and Levine medication adherence scale		✔	✔	✔	✔	✔	✔	✔	✔
MTBQ		✔	✔	✔	✔	✔	✔	✔	✔
Diet Management		✔	✔	✔	✔	✔	✔	✔	✔
Fried frailty index	✔	✔	✔	✔	✔	✔	✔	✔	✔
6MWT	✔	✔	✔	✔	✔	✔	✔	✔	✔
Modified Borg dyspnoea scale	✔	✔	✔	✔	✔	✔	✔	✔	✔
Hand grip strength	✔	✔	✔	✔	✔	✔	✔	✔	✔
Specific activity questionnaire		✔	✔	✔	✔	✔	✔	✔	✔
Borg scale of perceived exertion		✔	✔	✔	✔	✔	✔	✔	✔
weight management		✔	✔	✔	✔	✔	✔	✔	✔
EQ-5D-5L	✔	✔	✔	✔	✔	✔	✔	✔	✔
Responsiveness to change		✔	✔	✔	✔	✔	✔	✔	✔
Family support		✔	✔	✔	✔	✔	✔	✔	✔
Responsiveness assessment		✔	✔	✔	✔	✔	✔	✔	✔
Patient satisfaction in quality of care	✔	✔	✔	✔	✔	✔	✔	✔	✔
CTM-3	✔				✔		✔		✔
B-prepared scale	✔								
Treatment expenditure questionnaire			✔		✔		✔		✔

PHQ-9- Patient Health Questionnaire- 9, KCCQ-Kansas City Cardiomyopathy Questionnaire, GAD-7- Generalised Anxiety Disorder Questionnaire, MTBQ- Multi-morbidity Treatment Burden Questionnaire, 6MWT- Six Minute Walk Test, CTM-3- Care Transitions Measure

*Study intervention overview*

All patients receiving care at a unit randomised to the usual care arm will receive the same standard of care, while all patients receiving care at units randomised to the intervention arm will receive the CCM based care.

Usual care arm: The treating physician will provide care for patients at the units that are randomised to the usual care arm. However, the physician will be assisted by a clinical coordinator to capture relevant demographic, clinical and biochemical variables of interest, and data regarding cost of care, patient satisfaction, and quality of life by using a structured interview schedule.

Intervention arm: The intervention will leverage the existing management practices at each site to deliver a comprehensive, integrated HF care led by a trained nurse with support from physicians, dieticians, physiotherapist, and clinical psychologists (
Figure 1). Information from the formative research will be scientifically integrated into the comprehensive management programme. The nurses will be enabled with mHealth technology to facilitate care delivery.

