**Trial sample size and power**

The mean difference in DAOH was assumed to be 20 days (586 Vs 566 days with a standard deviation of 69 days) at two-year. We used the DAOH at two-year from the Trivandrum Heart Failure Registry in the sample size calculation
^
7
^. In the intervention group, we assumed 3% higher DAOH. A sample size of 770 HF participants per group (a total of 1540), in 11 equal clusters per arm (total 22 clusters) provides 91% power for a 2-sided 5% alpha. Assumptions; an ICC of 0.01 (design effect 2.08), coefficient of variation of cluster size of 0.85.

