**Data analysis plan**

Aim1: All interviews conducted in local language (Malayalam) will be simultaneously translated to English and transcribed. Interviews conducted in English language will be transcribed. The data analysis will follow a framework method of analysis
^
55
^. After the data is transcribed, the transcripts will be read line-by-line to get familiarised with the data. First a few transcripts will be coded using an inductive method. Later, a working analytical framework will be generated by merging the initial codes. The working analytical framework will then be used to index the remaining interviews. After indexing all the interviews, key themes will be generated by merging categories having similar meaning for each stakeholder. Finally, the data will be interpreted based on the convergences and divergences between the data themes across different stakeholders.

 Aim 2: All quantitative analysis will follow guidelines of cluster randomised trials
^
56
^. We will employ intention to treat analysis except in the sub-group analyses. Initially, baseline characteristics will be compared by treatment group to examine the adequacy of randomisation. The primary analysis will be a complete case analysis. However, missing data on outcome variables will be reported and sensitivity analyses will be conducted after multiple imputation of missing data.

The DAOH will be calculated by subtracting days in hospital and days from death until end of study follow-up from the total follow-up time of 730 days. The DAOH is a patient-centred outcome, which accounts for multiple events over the two-year course of a study period, weighs death more than hospitalisation, and deaths occurring early more than those occurring later. Empirical density curves will be created to show the distribution of DAOH over two-year follow-up period, stratified by intervention group. The median and the interquartile range of DAOH by treatment group will be provided. Poisson regression with a robust variance estimate
^
57
^ and an offset term to account for clustering will be employed in the analyses of DAOH per two-years of follow-up time. This procedure will yield a rate ratio and 95% CI
^
57
^. The rate ratio is the DAOH in the intervention arm divided by DAOH in the enhanced usual care arm. A rate ratio of >1 indicates more DAOH in the intervention arm in comparison to the usual care arm (i.e., favours the intervention).

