Multilevel mixed-effects survival models will be employed for analyses of time to secondary outcomes (composite of mortality and hospitalisation). A random term identifying the location of participating sites will account for the clustering effect. We will also conduct a landmark analysis conditional upon intervention group membership at 30 days of follow-up. The between-group differences for each of the secondary outcomes (other than binary outcomes variables) will be measured using mixed-effect linear models and after accounting for clustering of observations. Standard errors will be calculated using robust estimation procedures
^
58
^.

Pre-specified sub-group analyses (age group, sex, region, type of facility, clinical severity) will be conducted. The significance of subgroup effects will be assessed by tests of interactions of covariates and the treatment effect.

Finally, as an exploratory analysis we will also use win ratio
^
59
^ to analyse the composite secondary outcome of mortality and hospital admissions. The win ratio statistic prioritises the mortality and hospitalisation endpoints through sequential comparisons. Patients in the intervention and usual care group will be converted into matched pairs based on their baseline risk profiles. The intervention patient will be labelled as a ‘winner’ or a ‘loser’ depending on who died first. If there is no death, the pairs will be labelled a ‘winner’ or ‘loser’ depending on who had a hospitalisation first. Otherwise, they are considered tied. Finally, the win ratio will be generated, which is the total number of winners divided by the total numbers of losers. A 95% confidence interval and
*P*-value for the win ratio will be obtained. If matched pairs are not possible; the analyses will be conducted on unmatched pairs.

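### Twenty-two hospitals are allocated with no balancing on site features and the printed models name no baseline covariate, which gives up precision although the baseline values are collected

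*Protocol article*

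**What the plan says.** On allocation, the Study design approach section says: "Eligible units will be randomised at one time point, prior to trial implementation", "The allocation ratio will be 1:1", and "Randomisation procedures will not be blocked, restricted, or matched". It adds: "We will use computer generated random numbers to allocate half of the units to each arm of the study". Arm size is therefore fixed at 11 hospitals each, as the sample size section also assumes ("in 11 equal clusters per arm (total 22 clusters"), but no site feature is balanced by design.

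On analysis, the Data analysis plan (Aim 2) begins: "Initially, baseline characteristics will be compared by treatment group to examine the adequacy of randomisation". It then gives Poisson regression with robust variance and an offset for DAOH, and mixed-effects survival models with a random site term for time to the composite outcome. For the remaining secondary outcomes the text reads: "other than binary outcomes variables) will be measured using mixed-effect linear models and after accounting for clustering of observations". None of these descriptions names a baseline covariate.

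On data, Measurements in the study and Table 3 list 6MWT, KCCQ-12, EQ-5D-5L, frailty, grip strength and blood pressure at baseline, with demographics and aetiology in the baseline questionnaire. Study outcomes lists walking distance and quality of life as major secondary outcomes. Region, type of facility and clinical severity appear as subgroup factors, from which one infers that they are recorded.

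**The concern.** With 11 hospitals per arm, features such as facility type or region can fall unevenly by chance. Nothing in the allocation guards against this, and nothing in the printed primary model corrects for it. The baseline comparison is given no stated consequence for the analysis. A reader who sees an uneven baseline table would then have only an unadjusted estimate or an adjustment chosen after the fact.

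The second cost does not depend on imbalance. Earlier values of 6MWT and quality of life usually predict later ones, so a model that omits the baseline value carries patient-level variance that could be removed. For DAOH, age and severity markers may do the same to a smaller degree.

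**Working it through.** **Inputs.** From Trial sample size and power: 770 patients per arm, 11 clusters per arm, difference 20 days (586 vs 566), SD 69 days, design effect 2.08, ICC 0.01, two-sided 5%, stated power 91%; the same section also gives the effect as 3%. Assumed, because the article gives no figures: the number of hospitals with a given feature, the R² of the covariates, and the baseline–follow-up correlation r. The calculation is on the day scale of the sample size section, as an approximation to the Poisson analysis.

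**1. The plan's own power.** SE = 69 × √(2 × 2.08/770) = 5.07 days.
- 20 days: 20/5.07 − 1.96 = 1.98, power 97.6% (normal); 96.3% with t on 22 − 2 = 20 df.
- 3% of 566 = 16.98 days: 16.98/5.07 − 1.96 = 1.39, power 91.7% (normal); 88.9% with t on 20 df.

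The stated 91% is close to the 3% effect and is not reproduced with 20 days. Neither reading shows low power.

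**2. Chance of an uneven split.** There are C(22,11) = 705,432 equally likely allocations.
- Feature in 6 hospitals, 5:1 or worse: 2 × [C(6,5)C(16,6) + C(6,6)C(16,5)] = 2 × (48,048 + 4,368) = 104,832; probability 14.9%.
- Feature in 8 hospitals, 6:2 or worse: 2 × [C(8,6)C(14,5) + C(8,7)C(14,4) + C(8,8)C(14,3)] = 2 × (56,056 + 8,008 + 364) = 128,856; probability 18.3%.
- Feature in 11 hospitals: 7:4 or worse 39.5%; 8:3 or worse 8.6%.
- Any continuous hospital-level characteristic: the standardised difference between arms has SD √(2/11) = 0.43.

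**3. What such a split does.** With equal cluster sizes, a 5:1 or a 6:2 split moves the arm contrast by 4/11 = 36% of the difference in mean DAOH between the two kinds of hospital. The ICC implies a between-hospital SD of 69 × √0.01 = 6.9 days. If the two kinds differed by that amount (an assumption), the shift would be 4/11 × 6.9 = 2.5 days, about half of the 5.07-day SE.

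**4. Gain for DAOH.** Adjusted SE = 5.07 × √(1 − R²), taking R² to apply equally within and between hospitals.

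| Assumed R² | SE (days) | Power if the unadjusted power is the stated 91% |
|---|---|---|
| 0% | 5.07 | 91.0% |
| 10% | 4.81 | 93.6% |
| 20% | 4.54 | 95.8% |

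The last column is Φ[(1.960 + 1.341)/√(1 − R²) − 1.960].

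**5. Gain for 6MWT and quality of life.** The share of patient-level variance removed is r²: 0.5² = 25% to 0.6² = 36%. The patient-level SD falls to √0.75 = 0.87 or √0.64 = 0.80 of its value. The gain in the SE of the arm difference is smaller if between-hospital variance is not reduced to the same degree.

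**6. Price in degrees of freedom.** At SE 5.07 and 20 days, power is 96.3% on 20 df, 96.2% on 19 and 96.1% on 18: less than 0.2 points for two hospital-level terms.

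**The case against.** The strongest reply is that the article is silent on covariates rather than opposed to them. It names model families, a condensed article commonly leaves the covariate list to the SAP, and the SAP may already contain one. This stands, and it limits the point to the models as printed. It does not remove it: the same section goes into subgroup factors, a landmark analysis and win-ratio matching on baseline risk, yet gives the main models no baseline term.

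Second, simple allocation is legitimate and unbiased, and a cluster-level standard error already covers chance imbalance. That stands. Eligibility also narrows site differences: heart failure centres of major hospitals from two registries, with a minimum patient volume and similar team roles. A reader might infer that sizeable imbalance is likely or that the rate ratio is biased. The documents support neither: the 15% and 18% rest on assumed counts.

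Third, a reader might add that the trial has low power and so cannot afford the loss. The article's own inputs give about 96–98% for 20 days and 89–92% for a 3% effect.

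Fourth, patients consent after their hospital is allocated in an open-label trial, and one might expect adjustment to remove any resulting selection. It cannot do so for unmeasured differences. Consecutive recruitment is the stated safeguard, and recruitment bias is a separate question.

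Finally, baseline data are not wholly unused: they enter the subgroup tests and the exploratory win ratio. They are absent from the primary and main secondary comparisons as printed.

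**Conclusion.** The point holds as one of efficiency and prespecification. An 11:11 allocation of 22 hospitals with no balancing on site features is followed by printed models without baseline terms, where better models are available from data already planned. For DAOH the gain is moderate: an SE of about 4.8–4.5 instead of 5.07 days at an assumed R² of 10–20%. For 6MWT and quality of life it is larger: 25–36% of patient-level variance at an assumed r of 0.5–0.6. Protection against an uneven hospital split matters in roughly 15–18% of allocations under the assumed counts of 6 or 8 hospitals. The plan should be changed on this point, but nothing here invalidates the design, biases the comparison or shows the trial to be underpowered.

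**What to change.** The allocation stays as it is: hospitals are randomised before implementation and Study status reports that recruitment has started. Before any outcome data by arm are seen:

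- Include the baseline value in each mixed model for 6MWT, KCCQ and EQ-5D-5L.
- Prespecify a short covariate set for the DAOH model, for example age, sex, one baseline severity marker, and at most one or two hospital-level terms such as facility type.
- Make the adjusted estimate primary and report the unadjusted one as supportive.
- Use the baseline table to describe the arms, and state that it will not decide whether to adjust.

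If the SAP already says this, confirm it and no change is needed.

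The cost is wording, plus two practical matters. The primary analysis is complete-case, so missing baseline values need a simple imputation rule, set without regard to arm, or patients will be lost. Hospital-level terms use one or two of about 20 df; region may need more than one term, which is a reason to choose sparingly.
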